## Abstract

**Introduction:**

Total knee arthroplasty (TKA) surgery causes postoperative pain. The use of perioperative injections around the knee containing local anaesthetic, opiates and non-steroidal anti-inflammatory drugs has increased in popularity to manage pain. Theoretical advantages include reduced requirements for analgesia and earlier mobilisation. We propose a single-centre randomised controlled trial of multimodal periarticular anaesthetic infiltration versus femoral nerve anaesthetic blockade as analgesia for TKA. The aim is to determine, in patients undergoing TKA, if there is a difference in patient-reported pain scores on the visual analogue scale (VAS) prior to physiotherapy on day 1 postoperatively between treatment groups.

**Methods and analysis:**

Patients undergoing a primary unilateral TKA at University Hospitals Coventry and Warwickshire Hospitals will be assessed for eligibility. A total of 264 patients will provide 90% power to detect a difference of 12 mm on the VAS on day 1 postoperatively at the 5% level. The trial will use 1:1 randomisation, stratified by mode of anaesthetic. Primary outcome measure will be the VAS for pain prior to physiotherapy on day 1. Secondary outcome measures include VAS on day 2, total use of opiate analgesia up to 48 h, ordinal pain scores up to 40 min after surgery, independent functional knee physiotherapist assessment on days 1 and 2. Oxford knee Scores (OKS), EuroQol (EQ-5D) and Douleur Neuropathic Pain Scores (DN2) will be recorded at baseline, 6 weeks and 12 months. Adverse events will be recorded up to 12 months. Analysis will investigate differences in VAS on day 1 between the two treatment groups on an intention-to-treat basis. Tests will be two-sided and considered to provide evidence for a significant difference if p values are less than 0.05.

**Ethics and dissemination:**

NRES Committee West Midlands, 23 September 2013 (ref: 13/WM/0316). The results will be disseminated via peer-reviewed publications and conference presentations.

**Trial registration numbers:**

ISRCTN 60611146 and EUDRACT Number 2013-002439-10 (protocol code number PAKA-33601-AS117013); Pre-results.

Strengths and limitations of this studyPragmatic design to facilitate implementation within routine clinical practice.Optimised protocol to reduce risk of bias.Appropriate sample size calculation and a planned intention-to-treat analysis.Lack of blinding among clinicians delivering the intervention.Single-centre design.

## Introduction

Total knee arthroplasty (TKA) is the commonest joint replacement, with over 82 000 procedures performed annually in the National Health Service (NHS).^1^ Demand is growing and this, combined with an ageing population, the frequency of TKA and its burden on the NHS increases year on year. During the last decade, there has been increased interest in optimal perioperative care to enhance recovery following TKA. Improvement of analgesia; reduction of surgical stress responses and organ dysfunctions; including nausea, vomiting and ileus; early mobilisation; and oral nutrition have all been examined. Measures to try and improve pain management have been developed including multimodal regimes which theoretically allow functional rehabilitation to be initiated more rapidly postoperatively. TKA generates substantial amounts of postoperative pain, which effects range of movement and ability to mobilise. Good pain relief with minimal physiological disturbance is important for postoperative knee rehabilitation.^2–4^ Epidural analgesia is very effective in pain control but is associated with side effects such as pruritus, urinary retention and motor block.^2^ Epidural analgesia can also occasionally lead to serious complications such as spinal cord ischaemia, vertebral canal haematoma, vertebral canal abscess, infective meningitis, nerve and spinal cord injury, wrong route administration and cardiovascular collapse.^5^

The use of opioid drugs, administered by means of either patient-controlled analgesia or other methods, is another effective method of postoperative pain relief but is often associated with systemic side effects, including nausea and vomiting, respiratory depression, drowsiness, pruritus, reduced gut mobility, and urinary retention.^6^ Drowsiness in particular may delay the patient's postoperative mobilisation. Femoral nerve block, as a single perioperative infiltration or via an indwelling catheter, has been shown to improve postoperative pain control and reduce the use of systemic analgesics and is currently the standard care for perioperative analgesia.^7^ The key advantage of the technique is that it avoids the systemic effects associated with both epidural and opioid analgesics. However, it may be associated with complications such as vascular puncture, nerve damage, infection and diminished muscle control.^8^ The inhibition of the quadriceps muscle group can delay postoperative mobilisation.^9^ Since the posterior capsule of the knee joint is innervated by the branches of the sciatic nerve rather than the femoral, femoral nerve blockade may also result in incomplete pain relief. Femoral nerve block is currently the standard perioperative analgesia for TKR surgery among anaesthetists working within the NHS.

Recently the use of intraoperative, periarticular infiltration of multimodal analgesics has gained in popularity. Periarticular infiltration has the advantage of delivering drugs directly to the sources of pain, thereby avoiding systemic side effects.^10^ The concept of multimodal analgesia refers to the simultaneous administration of multiple anaesthetic agents, such as local anaesthetics, opiates and non-steroids anti-inflammatory drugs (NSAIDs). To produce optimal pain relief combined with the lowest incidence of side effects, a multimodal pain therapy is essential.^5^ This technique of analgesia was developed specifically to avoid sedation and facilitate rapid physiological recovery after lower limb arthroplasty in order to enable early mobilisation and discharge.^9–13^ In contrast to femoral nerve blockade, periarticular infiltration does not inhibit quadriceps function and also reaches the posterior capsule of the knee joint. Published studies suggest that periarticular infiltration may reduce requirements for postoperative analgesia, lead to earlier mobilisation and discharge from hospital. However, the number of published randomised controlled trials involving TKA is small and all are underpowered and lack statistical rigour. An initial pilot study comparing femoral nerve block and multimodal periarticular infiltration has already been completed in order to help plan and design a full trial with the following null hypothesis.^14^

Postoperative pain following primary TKA does not differ between multimodal periarticular knee infiltration with levobupivacaine 150 mg, morphine 10 mg and ketorolac 30 mg diluted in 0.9% saline to make a volume 100 mL (0.5 mL 1:1000 epinephrine) and the single-agent femoral nerve blockade.

These two comparators have been chosen for comparison because femoral nerve block is the current standard care for perioperative analgesia for TKR surgery and multimodal periarticular infiltration represents a new but now established alternative.

## Objectives

The primary objective of this full trial is to quantify and draw inferences on the efficacy between treatment groups based on observed differences as shown by a validated, patient-reported 100 mm visual analogue pain score, prephysiotherapy on the first postoperative day, collected by an independent physiotherapist. This is the most important outcome as pain at the time when the patient is first starting to walk and use their new knee replacement will determine the ability of the patient to mobilise. Early mobilisation is associated with improved functional outcomes and a reduced risk of complications.^15^

The secondary objectives of the study are to quantify and draw inferences on the efficacy of the treatment groups based on observed differences as shown by:
Visual analogue scale (VAS) after physiotherapy on the first postoperative day and before and after physiotherapy on the second postoperative day.The total use of opiate analgesia up to 24 and 48 h after the operation.Ordinal pain score (routinely collected up to 40 min after surgery).Independent routine functional physiotherapist assessment on days 1 and 2 postoperatively assessing: straight leg raise (SLR), knee range of movement, Timed Up and Go (TUG), bed transfers and distance mobilised.Oxford Knee Score (OKS) collected preoperatively and 6 weeks postoperatively.EuroQol (EQ-5D-5L) Score collected preoperatively and 6 weeks postoperatively.Douleur Neuropathic Pain Scores (DN2/seven-item DN4) collected preoperatively and 6 weeks and 12 months postoperatively.^16^
^17^The number and type of adverse events (AEs) up to 12 months postoperatively.

## Methods and analysis

The protocol (V.5.0 dated 7 October 2015) was prepared in accordance with the Standard Protocol Items: Recommendations for Interventional Trials (SPIRIT) guidelines.^18^ This study is jointly sponsored by the University of Warwick and University Hospitals Coventry and Warwickshire NHS Trust. The trial will be carried out in accordance with the Medicines for Human use (Clinical Trials) Regulations 2004 (SI 2004/1031), amended regulations (SI 2006/1928) and the International Conference on Harmonisation Good Clinical Practice (ICH-GCP); all collaborators will be trained in GCP, and in accordance with this protocol. This trial will be reported in line with the Consolidated Standards of Reporting Trials (CONSORT) statement.

A single-centre two-arm parallel group superiority type trial design will be completed. All patients undergoing an elective primary unilateral TKA under the care of an orthopaedic consultant at University Hospitals Coventry and Warwickshire NHS Trust are potentially eligible for entry to the trial. However, patients with any of the following will not be eligible:
Concomitant medical or psychiatric problems which, in the opinion of the investigator, would prevent completion of treatment or follow-up.Preoperative history of neurological abnormality in the ipsilateral leg, for example, history of stoke, neurogenic pain or previous nerve pain.Specific contraindication to the analgesic agents used:
*Morphine*
i. Hypersensitivity reaction.*Ketorolac*
i. Active or previous peptic ulcer;ii. History of upper gastrointestinal bleeding or perforation, related to previous NSAID therapy;iii. Haemorrhagic diatheses, including coagulation disorders;iv. Hypersensitivity to ketorolac, trometamol or other NSAIDs;v. Moderate or severe renal impairment (serum creatinine >160 μmol/L).*Levobupivacaine*
i. Known hypersensitivity to levobupivacaine, local anaesthetics of the amide type or any of the excipients;ii. Uncontrolled angina;iii. Second or third degree heart block.Participation in a clinical trial of an investigational medicinal product (IMP) in the past 90 days.Previous entry in the present trial.Evidence that the patient would be unable to adhere to trial procedures.

Patients fulfilling the eligibility criteria will be identified by consultants and research associates in outpatient clinics. In order to ensure all eligible patients are approached for recruitment patients already on the waiting list (as identified via hospital operative planning software, Opera) for a unilateral TKA will be screened and may be contacted during their preoperative assessment at the hospital, which normally occurs a few weeks before surgery. All appropriate patients will be approached as per ICH-GCP guidelines. Patients will be recruited by trained research associates who will help to present the trial and interventions in a consistent and unbiased manner. Recruitment by trained research associates will also be a mechanism to help ensure optimum participant enrolment.^19^ Patients will only be given ‘Letters of Invitation’ if, in the opinion of the research associate, there has been an adequate verbal introduction to the trial. Patients will be given adequate time to consider their participation in order to ensure informed consent to participate in the trial. Signed and dated informed consent will be obtained by medically trained personnel as per trust protocol for Clinical Trial Investigation of a Medicinal Product (CTIMP) study. In the event that any further information becomes available, which may influence the patient's willingness to continue in the trial, the trial team will contact the participant. The participant's general practitioner (GP) will be informed by letter that the patient is taking/has taken part in this clinical trial. A participant may deny the research team permission to inform the GP of their trial involvement by not initialling the appropriate box on the consent form. Prerandomisation eligibility checks will be carried out to ensure that a patient fit the eligibility criteria and is not randomised in error. Inclusion of a patient in the trial will be flagged on their clinical notes by means of a trial sticker.

## Randomisation

Allocation of trial treatments will be provided through a distal randomisation service. Randomisation will be a 1:1 allocation using a computer-generated randomisation schedule stratified by anaesthetic type—general or spinal block using permuted blocks of random sizes. The block sizes will not be disclosed, to ensure concealment. To ensure allocation concealment, the mechanism of contact being used is via a telephone and has a stringent procedure to ensure enrolment before randomisation. Randomisation via telephone will be undertaken by a trained member of the theatre team present on the day of surgery. They will then inform the rest of the theatre team (excluding the participant) of the treatment allocation.

## Sample size

The primary outcome measure for this study is pain on day 1 postoperatively, assessed using a 100 mm VAS. Pilot data (n=46) were used in a power analysis to estimate the sample size required for a two-arm parallel group RCT. Based on the available literature, a change in the VAS of 12 mm (95% CI 9 to 15) is clinically meaningful; thus, these calculations assume the minimum clinical important difference (MCID) to be approximately 12 mm.^20^ The observed SD from the pilot study was 30 mm, giving a standardised effect size (MCID/SD) of 0.4, a moderate value, and of the appropriate order of magnitude for a pragmatic study of this type. Hence, to power a trial to test the null hypothesis of equality of the treatments, assuming approximate normality for the VAS, would require 132 patients in each treatment arm or 264 in total—assuming 90% power, 5% significance, a SD of 3 cm and an MCID of 12 mm. Given that the majority of data collection will occur during participant hospital stay, with the exception of the patient-reported outcome measures, we anticipate loss of follow-up data will be minimal (<5%). The sample size for this trial corresponds to effects observed in previous similar studies.^20^
^21^ These studies demonstrated effects on a 100 mm VAS (our primary outcome measure) and on participant consumption of ‘as required’ analgesia with 20–25 patients per experimental group.

Recent audit within the department indicated there are approximately 50 elective primary unilateral total knee replacements carried out per month, of whom over half would be eligible for this trial. Although not all patients will want to take part, our previous experience in trials of perioperative adjuncts to surgery has shown high levels of patient recruitment (80–100%) with only 7% declining the pilot study. Therefore, we believe 11 patients per month to be a realistic recruitment figure. At this rate, the entire study sample can be recruited within 24 months. However, if recruitment rate is not as high as anticipated, a sample size of 200 patients will still be adequate to identify any difference between groups with 80% power.

Participants may withdraw from the trial treatment and/or the whole trial at any time without prejudice. Unless a participant explicitly withdraws their consent, they should be followed-up and data collected as per the protocol until the end of the trial.

Should a participant withdraw from the trial, they would continue to be treated as per normal routine postoperative management, follow-up and clinical practice. The data collected up until the point of withdrawal would be used for analysis at the end of the trial. Participants may be withdrawn from the trial at the discretion of the investigator and/or the Trial Steering Committee (TSC) due to safety concerns.

## Blinding

Patients will be blind to the intervention to which they are allocated, as femoral nerve blocks will be done after sedation and or anaesthetic. All interventions will be conducted within a sterile zone with drapes which will physically prevent patients seeing which intervention they receive. Owing to the nature of the study, it is not possible for the surgeon and anaesthetist delivering the interventions to be blinded to the treatment options. Outcome data will be collected by a research associate and an independent clinical physiotherapist who are blinded to the treatment allocation. Furthermore, the trial statistician will be blinded to the treatment allocations throughout.

## Interventions

In this pragmatic trial, patients will undergo routine elective primary unilateral TKA using the standard technique of the anaesthetist and the operating surgeon. In addition, the patient will receive one of the following perioperative analgesic interventions:
Femoral nerve block

Under aseptic conditions, the femoral artery will be palpated immediately below the inguinal ligament and nerve stimulation and or ultrasound will be used to identify the femoral nerve just lateral to the artery. Once the femoral nerve has been identified, the block may be performed in the routine manner (15, 16) using 30 mL (75 mg) of levobupivacaine hydrochloride 0.25%.
Intraoperative periarticular injection

The periarticular infiltration of multimodal agents will involve the preparation of two 50 mL syringes each containing 30 mL (75 mg) of levobupivacaine hydrochloride 0.25% injection, 0.5 mL (5 mg) morphine sulfate injection, 0.5 mL (15 mg) ketorolac trometamol injection and 0.25 mL of 1:1000 epinephrine then diluted with 0.9% saline to make a mixture containing a total volume of 50 mL. Epinephrine is added to the mixture to reduce blood loss after the operation. Each syringe will be prepared for immediate use and not stored. Fifty millilitre of the mixture will be injected into the posterior, medical and lateral soft tissues just prior to implantation of the TKR components. Care will be taken to avoid excessive infiltration in the area of the common peroneal nerve. Then, while the cement is curing, the anterior soft tissue including the quadriceps mechanism, the retinacular tissues and the subcuticular tissues will be infiltrated with the remaining 50 mL of periarticular injection.^13^ Following wound closure, the tourniquet will be released and the ‘tourniquet-down time’ noted on the trial documentation.

The allocated intervention will be discontinued if there is evidence of an immediate serious adverse reaction such as anaphylaxis. Once randomised if a participant specifically requested that the intervention was discontinued or modified this would be honoured provided valid consent was obtained; however, as both interventions are delivered perioperatively such a scenario is extremely unlikely.

A routine preoperative, perioperative and postoperative analgesic medicines regimen will be used for all of the participants following hospital guidelines for TKR surgery:

*Premedication (before surgery)*
1. Gabapentin 300 mg (100 mg if older than 70 years or chronic kidney disease (CKD) stage 3).

*Perioperatively*
1. Spinal: 2 mL of 0.5% heavy bupivacaine or 2 mL of 0.5% isobaric levobupivacaine (chirocaine).2. Sedate with target-controlled infusions of propofol or general anaesthetic if needed.3. If unable to do a spinal, use intravenous morphine 0.1–0.2 mg/kg intraoperatively.4. Paracetamol: 1 g intravenous.

*Postoperatively*
1. Paracetamol 1 g four times a day;2. Diclofenac 50 mg or ibuprofen 400 mg three times a day if no contraindications and to be started 8 h postoperatively;3. Gabapentin 300 or 100 mg three times a day for 5 days (lower dose for the over 70 s or CKD stage 3);4. Morphine sulphate tablets (MST) 20 mg twice daily for 5 days or until needed first dose in recovery before spinal wears off;5. Oramorph 10 or 20 mg (maximum hourly) as required.

*On discharge*
1. MST 10/20 mg twice daily (to cover 5 postoperative days);2. Gabapentin 300 mg three times a day (100 mg three times a day for over 70 s; to cover 5 days postoperative);3. Paracetomol 1 g four times a day;4. Ibuprofen/diclofenac 400 mg/50 mg three times a day.

All postoperative analgesia taken by the participants, both regular and as required (prn), will be recorded. All of the participants will follow the standard university hospitals coventry and warwickshire (UHCW) postoperative rehabilitation protocol under the supervision of a physiotherapist. This involves immediate full weight bearing with the use of crutches, no restriction in flexion and the regular use of a cryocuff for cold therapy.

The fidelity with which both interventions are delivered will be captured by regular audits against the standards described. The results will be relayed to those delivering the intervention in order to improve and/or maintain ongoing protocol compliance.

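### The discharge gabapentin line drops the CKD stage 3 dose reduction that the postoperative line sets for the same 5-day course

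*Protocol article*

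**What the plan says.** The Interventions section of the protocol article sets out background analgesia that applies to everyone: "A routine preoperative, perioperative and postoperative analgesic medicines regimen will be used for all of the participants following hospital guidelines for TKR surgery". Gabapentin appears three times in that list.

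- Premedication: "Gabapentin 300 mg (100 mg if older than 70 years or chronic kidney disease (CKD) stage 3".
- Postoperatively: "Gabapentin 300 or 100 mg three times a day for 5 days (lower dose for the over 70 s or CKD stage 3".
- On discharge: "Gabapentin 300 mg three times a day (100 mg three times a day for over 70 s; to cover 5 days postoperative".

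The only renal criterion for entry is in the exclusion list under Methods and analysis, among the contraindications to ketorolac: "Moderate or severe renal impairment (serum creatinine >160" μmol/L.

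**The concern.** The postoperative and discharge lines describe one course of treatment. The first sets the dose for 5 days and the second supplies the part of those 5 days that falls after the patient leaves hospital. The dose-reduction rule should therefore be the same in both. Instead the discharge line restates the rule with one of its two criteria missing. Because it spells out an exception for age, a prescriber would reasonably take the list of exceptions as complete.

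What is at stake is a renal dose safeguard that the protocol itself chose, lost when the patient leaves inpatient supervision. No other item in the discharge list carries a renal dose reduction. The randomised comparison is not at stake.

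**Working it through.** The plan gives no figure to reproduce. The check compares the three lines and then works out the doses.

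**Who gets the lower dose**

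| Line | Over 70 | CKD stage 3, aged 70 or under |
|---|---|---|
| Premedication | 100 mg | 100 mg |
| Postoperative, 5 days | 100 mg three times a day | 100 mg three times a day |
| Discharge, rest of the 5 days | 100 mg three times a day | 300 mg three times a day |

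The lines agree for participants over 70, whatever their renal function. They conflict only for those aged 70 or under with CKD stage 3.

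**Does the renal exclusion empty that group?** It is set by a serum creatinine threshold, not by CKD stage. It may remove some of these patients, but the article does not say that it removes them all.

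**Daily dose** (unit dose × 3)

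- Reduced: 100 × 3 = 300 mg/day.
- Full: 300 × 3 = 900 mg/day.
- Difference: 900 − 300 = 600 mg/day, a threefold dose.

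**Course total.** The intended course is 5 × 300 = 1500 mg. Length of stay is not stated, so the discharge day is an assumption. The earliest case taken is after day 2, because the Objectives section schedules "Independent routine functional physiotherapist assessment on days 1 and 2 postoperatively". With discharge after day *d*, the total is *d* × 300 + (5 − *d*) × 900.

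| Discharge after day | Total (mg) | Excess over 1500 mg | Ratio to intended |
|---|---|---|---|
| 2 | 2 × 300 + 3 × 900 = 3300 | 1800 | 2.2 |
| 3 | 3 × 300 + 2 × 900 = 2700 | 1200 | 1.8 |
| 4 | 4 × 300 + 1 × 900 = 2100 | 600 | 1.4 |
| 5 | 5 × 300 = 1500 | 0 | 1.0 |

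**The case against.** The best defence is that the postoperative line already fixes the rule for the full 5 days and is not limited to the inpatient stay, so the discharge line is only shorthand for the same course. The discharge list is visibly abbreviated elsewhere: its NSAID item drops the caveat about contraindications that the postoperative item carries, and nobody would suppose that contraindicated patients are meant to start NSAIDs at home. Gabapentin is also background care given under a hospital guideline that is not shown, and it is not one of the trial's investigational products. A prescriber may well apply the right dose. The affected group needs CKD stage 3, age 70 or under, creatinine not above the exclusion threshold and discharge before day 5, and it could be very small or empty. No harm from one to three days at the higher dose is demonstrated.

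Much of this stands. It makes a drafting slip far more likely than an intended change of dose, and it limits the severity. It does not remove the conflict. Even if the fuller line is meant to govern, the discharge instruction gives the wrong dose when followed as printed. If the guideline contains the CKD reduction, the article transcribes it wrongly. If it does not, the guideline disagrees with the other two lines. Nor is this detail left to another document, since the criterion is printed twice and dropped once.

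**Conclusion.** The concern holds, as a minor inconsistency with a patient-safety aspect. For a participant aged 70 or under with CKD stage 3, two lines of the same regimen give 300 mg/day and 900 mg/day within one 5-day course. That threefold difference comes directly from the text. The course multiples of 1.4 to 2.2 rest on two assumptions: that the discharge line is followed literally, and that discharge falls after day 4 at the latest and day 2 at the earliest. How many participants are exposed cannot be worked out from the article.

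Both arms receive the same regimen and the discrepancy begins only at discharge. The day 1 pre-physiotherapy VAS, the sample size and the analysis are unaffected.

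**What to change.** In the discharge gabapentin item, add *or CKD stage 3* after the over-70s criterion, so that it matches the postoperative item. Check the corrected line against the hospital guideline and the discharge prescription actually in use.

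The cost is four words and one check. Sample size, delivery of the randomised interventions and analysis do not change.
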